### General analytic approach

We hypothesize that self-reported 7-day point prevalence abstinence rates will be greater in MAPS + than in ST. All data analyses will be performed using SAS version 9.4 with significance set at 0.05 for statistical tests of primary hypotheses. Descriptive statistics will be used for initial review of distributions and determination of needs for transformation prior to primary analyses. Group differences in baseline measures will be assessed and any variable that exhibits a group difference at p < .10 will be added as a covariate in the primary analyses.

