### Procedures

This study was reviewed and approved by Advarra, the H. Lee Moffitt Cancer Center institutional review board (IRB) and is registered on ClinicalTrials.gov (NCT05645146). After completion of a brief online pre-screener, potential participants are contacted by research staff via phone to complete a more detailed screening. All eligible individuals are invited to participate. A detailed description of the study is provided, and verbal informed consent is obtained. Individuals who decline or are ineligible are referred to other cessation programs. Individuals who meet all eligibility criteria and consent to participating in the study complete the baseline assessment either over the phone with a research coordinator or via a secure electronic REDCap link sent via text message or email based on their preference. Following completion of the baseline assessment, participants are randomized to MAPS + or ST using a 1:1 ratio with a block size of 4 following stratification on the following variables: daily vs. nondaily smoking; CIN and early cancer stages (Stages I and Stage II) vs. advanced cancer stages (Stage III and Stage IV), and pending or in active treatment vs. completed treatment. The randomization sequences were created by the study statistician and implemented in REDCap.

Assessments occur at baseline, 3, 6, 12, 18 and 24 months and take approximately 20 min to complete (see Table 1). Participants are given the option to complete the assessments via phone or via a hyperlink as a REDCap-administered self-assessment. Compensation is provided after each assessment is completed (6 assessments x $30 = $180). Participants who report abstinence at any follow-up point are mailed a cotinine test. Compensation for returning cotinine tests is $30 per assessment.

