### Statistical analysis

#### Analytic plan for primary outcome

Logistic regression will assess treatment group differences in self-reported 7-day point prevalence abstinence at 24 months. Generalized estimating equations (GEE) will fit population-averaged models of longitudinally measured self-reported 7-day point prevalence abstinence, with the main covariates of treatment group, time (months from baseline), and the interaction of group and time. The GEE analysis permits evaluation of aggregated intervention effects across assessments, changes in abstinence over time, and group differences in changes (interaction term). These models will include any covariates found to differ by group (p < .10) despite randomization. Comparable models will be applied to evaluate treatment differences for secondary outcomes.

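### Covariates enter both primary models only on a chance baseline imbalance (p < .10), a rule that leaves the model unfixed and in practice never admits the three stratification factors

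*Protocol article*

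**What the plan says.** The section General analytic approach states that baseline group differences will be tested and that "any variable that exhibits a group difference at p < .10 will be added as a covariate in the primary analyses". The Analytic plan for primary outcome repeats the rule after describing the logistic and GEE models: "These models will include any covariates found to differ by group (p < .10) despite randomization".

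The fixed content of those models is short. For the 24-month model: "Logistic regression will assess treatment group differences in self-reported 7-day point prevalence abstinence at 24 months". For the GEE model, the terms are given "with the main covariates of treatment group, time (months from baseline), and the interaction of group and time". No baseline measure has a fixed place in either.

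Under Procedures, randomisation uses "a 1:1 ratio with a block size of 4 following stratification on the following variables: daily vs. nondaily smoking", then disease stage (CIN or early cancer against advanced cancer), and finally "pending or in active treatment vs. completed treatment". These three factors are named for randomisation only.

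**The concern.** In a properly randomised trial any baseline difference between arms is due to chance. A significance test of that difference says nothing about whether the variable predicts abstinence, and predicting abstinence is what makes a covariate worth adjusting for. The article itself describes several baseline measures as predictive of relapse or cessation outcome (the Heaviness of Smoking Index, self-efficacy, perceived stress, negative affect). Under the rule, each enters only if it happens to be unbalanced.

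Two things are at stake. First, the primary model cannot be written down before baseline data are seen, and the odds ratio it reports is conditional on whatever entered. Secondly, the precision available from prognostic covariates and from the stratification factors is left unused.

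**Working it through.** **1. The plan's own figure.** Inputs from Power and sample size: 170 per group, 16% against 29%, two-sided alpha 0.05. With pooled rate 0.225:

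- Null SE = √(2 × 0.225 × 0.775 / 170) = 0.0453. Alternative SE = √((0.16 × 0.84 + 0.29 × 0.71) / 170) = 0.0447.
- Power = Φ((0.13 − 1.96 × 0.0453) / 0.0447) = Φ(0.92) = 0.82.
- Wald test on the log odds ratio: log OR 0.763, SE 0.269, power Φ(0.763/0.269 − 1.96) = 0.81.

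The stated power of at least 0.80 reproduces with no covariates.

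**2. How many variables the rule admits.** With k independent variables screened at 0.10, the expected number entering is 0.1k and the chance of at least one is 1 − 0.9^k. Table 1 has 20 rows marked at baseline, several holding more than one variable. The article does not say which items or subscales count, so k is an assumption.

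| k | Expected entries | Chance of at least one |
|---|---|---|
| 20 | 2 | 88% |
| 30 | 3 | 96% |
| 40 | 4 | 98.5% |

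Correlation between measures changes the last column but not the expected count.

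**3. Whether the stratification factors can enter.** Three binary factors give 8 strata. With blocks of 4, each stratum can be out of balance by at most 2, so one level of a factor (4 strata) by at most 8. For a factor at an assumed 10% prevalence, that worst case gives z = (8/170) / √(2 × 0.10 × 0.90 / 170) = 1.45, below the 1.645 needed for p < .10. At 25% prevalence it gives 1.00. Only below about 7.5% could the worst case cross the threshold, and it would need all strata at maximum imbalance in the required directions. In simulation no stratification factor was selected in any of 4,000 runs per scenario.

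**4. Power.** Logistic regression on complete data was simulated with N = 340, stratified blocks of 4, marginal rates 16% and 29%, and 4,000 runs per scenario (Monte Carlo SE about 0.6 points). Assumed, because the article does not give them: factor prevalences 75%, 10% and 30%; 20 further variables screened, of which two may be prognostic; and the odds ratios shown.

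| OR per factor | OR per SD, two covariates | Unadjusted | p < .10 rule | Factors fixed | Factors and two covariates fixed |
|---|---|---|---|---|---|
| 1 | 1 | 0.817 | 0.812 | 0.819 | 0.819 |
| 1.5 | 1 | 0.822 | 0.811 | 0.830 | 0.827 |
| 2 | 1 | 0.827 | 0.818 | 0.841 | 0.837 |
| 3 | 1 | 0.834 | 0.825 | 0.855 | 0.852 |
| 1.5 | 1.5 | 0.828 | 0.823 | 0.834 | 0.851 |
| 2 | 1.5 | 0.833 | 0.824 | 0.844 | 0.856 |
| 2 | 2 | 0.830 | 0.830 | 0.839 | 0.880 |

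The rule never beats the unadjusted model. Against fixed factors it loses about 1 to 3 points, and against factors plus prognostic covariates up to 5. Simulations under other assumed strengths put the two ranges at 0 to 4 and 0 to 6 points.

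**5. Type I error.** Under the rule it was 0.046 to 0.052 in the four null scenarios completed, and 0.043 to 0.047 in a separate set. With the factors fixed it was 0.048 to 0.059. The highest value was at a factor OR of 3, so part of the apparent gain at that setting may be a slightly raised rejection rate.

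**6. Movement of the estimate.** With 40 independent screened variables, one stratification factor at OR 2, and two to four covariates at OR 1.5 per SD, the rule and the unadjusted model disagreed on significance at 0.05 in about 5% of simulated trials. The odds ratio moved by a median of 4 to 5%, and by about 13% or more in a tenth of trials.

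**The case against.** The best defence is that the rule is stated in advance, is mechanical and uses baseline data only, so outcome results cannot steer it. That stands. The model depends on chance, not on the analyst's choice, and its validity is intact.

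It can also be said that the article never excludes the stratification factors, and that adjusting for them is often left to an analysis plan that is not shown here. That stands too: their absence alone would not be a finding. What can be criticised is the written rule, which sets how covariates enter and in practice keeps these factors out.

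A reader might infer more than the documents support:

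- **False positives are inflated.** They are not; the simulated error rate stays near nominal.
- **The sample size statement is wrong.** It reproduces, and in every scenario tabulated power under the rule stays above 0.80 with complete data.
- **The power loss is large.** It is small, and near zero if the factors and covariates are not prognostic. The article gives no strength for any of them.
- **At least one entry is all but certain.** The 98.5% needs 40 independent variables. With the 20 rows of Table 1 it is 88%, and many of the measures are correlated.
- **Chance-selected covariates use up the events.** About 170 × (0.16 + 0.29) = 76.5 events are expected. Four chance entries plus treatment leave 76.5/5 = 15.3 per term, and a prespecified set of similar size leaves the same.
- **Noise covariates shift the odds ratio through non-collapsibility.** Only prognostic covariates do that.

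**Conclusion.** The point holds at moderate weight. The article fixes, in two places, a covariate rule for both primary models that selects chance imbalance instead of prognosis, leaves the covariate set open until baseline data are seen, and in practice never admits the factors used to stratify randomisation. That much follows from the text and the block design.

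The size of the power cost does not. It is about 0 to 6 points against prespecified adjustment and rests on assumed prognostic strengths and factor prevalences. The simulations cover the logistic model with complete data; the GEE model and multiple imputation were not simulated. The reason to change the rule is mainly that the primary estimate should have a conditioning set known in advance.

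**What to change.** - Delete the p < .10 rule from both sections.
- In the logistic and GEE models, include the three stratification factors regardless of imbalance, with a prespecified rule for collapsing sparse cells (the advanced-stage level is the likeliest).
- Add a short, fixed list of prognostic baseline measures already collected, for example the Heaviness of Smoking Index. The choice is the trial team's, but it should be made before outcome analysis.
- Report baseline characteristics descriptively, without tests.
- Keep the unadjusted analysis as a sensitivity analysis.

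The cost is wording only: no new data or participants, and the article describes recruitment as ongoing. The downsides are that the odds ratio becomes conditional on the chosen factors, and so no longer corresponds directly to the 16% against 29% contrast in the power statement, and that sparse strata may need collapsing.

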### Statistical analysis

#### Analytic plan for primary outcome

Logistic regression will assess treatment group differences in self-reported 7-day point prevalence abstinence at 24 months. Generalized estimating equations (GEE) will fit population-averaged models of longitudinally measured self-reported 7-day point prevalence abstinence, with the main covariates of treatment group, time (months from baseline), and the interaction of group and time. The GEE analysis permits evaluation of aggregated intervention effects across assessments, changes in abstinence over time, and group differences in changes (interaction term). These models will include any covariates found to differ by group (p < .10) despite randomization. Comparable models will be applied to evaluate treatment differences for secondary outcomes.

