**Fig. 1 Fig1:**
[figure not shown]
Study flow

ST participants are electronically connected with Tobacco Free Florida (i.e., the Florida Quitline). MAPS + consists of 6 proactive MAPS-based phone counseling sessions over 12 months plus a novel digital treatment adjuvant, which is delivered over 24 months. All participants receive 12 weeks of combination nicotine replacement therapy (patches + lozenges). Assessments are completed at baseline, 3, 6, 12, 18 and 24 months following baseline. All assessments are completed remotely (over the phone or via a secure REDCap link). In addition, brief REDCap-based smartphone assessments are delivered every 30 days, which are used to drive the personalized text-based treatment content in the MAPS + condition, are administered throughout the 24-month treatment period. These assessments are also delivered to ST participants to ensure that both treatment conditions are matched on assessment burden. The primary outcome is self-reported 7-day point prevalence abstinence over time throughout the 24-month assessment period [29, 30]. Secondary outcomes include additional smoking-related outcomes (i.e., biochemically verified abstinence, length of abstinence, continuous abstinence, cigarettes per day, quit attempts).

It is hypothesized that self-reported, 7-day point prevalence abstinence rates will be greater in MAPS + than in ST over time throughout the 24-month assessment period. For secondary outcomes, it is hypothesized that MAPS+ (vs. ST) participants will have higher biochemically confirmed abstinence rates at 24 months and across all assessments, make more quit attempts, report longer periods of abstinence, and report smoking fewer cigarettes per day across all assessments throughout the 24-month study period.

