### Recruitment and participants

Participant recruitment began in December 2022. Participants (target sample size = 340) are recruited through internet advertisements (i.e., Facebook, Instagram, Google pay-per-click ads, Craigslist) and internet-based, healthcare provider or community referrals (e.g., ClinicalTrials.gov, flyers, word-of-mouth). Inclusion criteria are: (1) ≥ 18 years of age; (2) ≥ 100 lifetime cigarettes; (3) English-speaking; (4) self-report of smoking ≥ 1 cigarette in past 30 days; (5) history of cervical cancer or CIN; (6) working smartphone; (7) valid home address; and (8) reside in Florida at the time of study enrollment. Exclusion criteria are: (1) medical condition precluding NRT; (2) currently receiving behavioral or pharmacological tobacco treatment; (3) household member enrolled in the study.

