### Nicotine replacement therapy

All study participants receive 12 weeks of combination nicotine replacement therapy (patches + lozenges). Nicotine patches provide a low, constant level of nicotine, which attenuates nicotine withdrawal symptoms, and lozenges help with managing acute cravings to smoke. When combined with behavioral treatment, NRT doubles the odds of successfully quitting [26]. All participants receive educational materials describing potential side effects, proper use of the patch, and an illustration demonstrating the proper placement of the patch on the body. The nicotine patch and lozenge regimens are based on each participant’s self-reported smoking rate. Participants who smoke > 10 cigarettes/day receive 8 weeks of 21 mg patches, 2 weeks of 14 mg patches, 2 weeks of 7 mg patches, and 12 weeks of 2 mg lozenges. Those who smoke < = 10 cigarettes/day receive 8 weeks of 14 mg patches, 4 weeks of 7 mg patches, and 12 weeks of 2 mg lozenges.

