**DEMOGRAPHICS, SMOKING, SUBSTANCE USE, HEALTH HISTORY**			
Demographics and Smoking History	X		
History of CIN or Cervical Cancer	X		
Medical Comorbidities	X		
Cancer Patient – Tobacco Use Questionnaire (C-TUQ)	X		X
Heaviness of Smoking Index (HSI)	X		
Wisconsin Index of Smoking Dependence (WISDM-37)			X
Substance Use History	X		
Alcohol Use History (NIAAA)	X		X
Subjective Social Status	X		X
Health Literacy	X		

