#### Demographics, smoking history, alcohol and substance use, and health history

Demographic variables assessed include age, race, ethnicity, education, income, gender identity, sex assigned at birth, marital status, sexual orientation, occupational status and insurance status. Smoking history is assessed by asking about years smoking, preferred brand of cigarettes, quitting history, partner smoking, and the presence of other people who smoke in the household. The use of e-cigarettes (vaping) is also assessed. History of alcohol use is assessed using NIAAA core items [35, 36]. Substance use history is assessed with three items asking about illegal substance use in the past year.

History of CIN or cervical cancer is assessed by asking about diagnostic history, dysplasia grade or cervical cancer stage at the time of diagnosis, current CIN or cervical cancer stage, time since diagnosis, treatment status and time since completion of treatment.

The *Cancer Patient Tobacco Use Questionnaire (C-TUQ)* is a 22-item self-report survey designed to capture information about tobacco use by cancer patients and cancer survivors. The items are specifically tailored to the trajectory of cancer diagnosis, treatment, and survivorship. The C-TUQ survey tool is divided into five domains and includes a Core (short form of 4 items) and an Extension. The questionnaire is intended to be administered at key time points during periods of cancer treatment and recovery [37].

Nicotine dependence is assessed using the *Heaviness of Smoking Index (HSI)*. The HSI comprises two items from the Fagerstrom Test for Nicotine Dependence (FTND): self-reported average number of cigarettes smoked per day (CPD) and time to first cigarette upon waking (TTFC). The HSI is a good indicator of nicotine dependence, has fair internal consistency and is predictive of smoking relapse [38].

*The Wisconsin Index of Smoking Dependence Motives – Short Form (WISDM-37)* comprises 37 items designed to assess 11 different motivational domains: affective enhancement, affiliative attachment, automaticity, loss of control, cognitive enhancement, craving, cue exposure/associative processes, social/environmental goads, taste/sensory properties, tolerance, and weight control [39, 40].

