#### Smoking abstinence

*Self-report smoking abstinence* assessments are based on recommendations from the Society for Research on Nicotine and Tobacco (SRNT) [30] and include abstinence assessments at all follow-up assessments. We are evaluating two point-prevalence abstinence measures: (1) no smoking during the previous 7 days, and (2) no smoking during the previous 30 days. Point-prevalence abstinence rates (intent-to-treat) will be estimated using generalized estimating equations.

*Biochemically verified abstinence.* Biochemically verified abstinence is assessed using saliva cotinine [29]. Participants who report 7-day point-prevalence abstinence at any follow-up assessment are mailed a prepaid envelope, instructions for providing a saliva sample, and a saliva collection kit. Research staff are available to speak with participants by phone and/or email should the participant have questions about the collection process. The participant is asked to return the sample via mail using a pre-paid envelope and, upon receipt of returned saliva samples, participants are compensated $30.

*Smartphone assessments*. All participants are asked to complete brief monthly assessments through REDCap (sent via SMS) for 24 months. For participants randomized to MAPS+, these 5-item monthly assessments are used to check in and offer personally tailored treatment content delivered via text messages and matched on both (1) areas in which participants indicate a need for support, and (2) smoking status, perceived stress, motivation, and self-efficacy. Participants randomized to ST also receive monthly assessments of smoking status, perceived stress, motivation, and self-efficacy (four items) to ensure that both treatment conditions are matched on assessment contacts. However, ST participants do not receive additional treatment after completing these monthly assessments.

*Primary and secondary outcomes*. Our primary outcome is self-reported 7-day point prevalence abstinence at 24 months where participants who report no smoking in the previous 7 days are considered abstinent. This follows recommendations for community-based smoking cessation trials that do not involve in-person assessments [29, 30]. Secondary outcomes are biochemically verified abstinence, length of abstinence, continuous abstinence, cigarettes per day, and quit attempts.

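### Baseline cigarettes per day is not a prespecified covariate for the cigarettes-per-day outcome and enters the model only on chance imbalance, which gives away precision

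*Protocol article*

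**What the plan says.** CPD is a secondary outcome (protocol article, Smoking abstinence): "Secondary outcomes are biochemically verified abstinence, length of abstinence, continuous abstinence, cigarettes per day, and quit attempts". It has a directional hypothesis (Study design overview): MAPS+ participants are expected to "report smoking fewer cigarettes per day across all assessments throughout the 24-month study period".

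A graded pre-treatment value exists. The Measures section describes the Heaviness of Smoking Index (HSI) as comprising "self-reported average number of cigarettes smoked per day (CPD) and time to first cigarette upon waking (TTFC"), and Table 1 schedules the HSI at baseline only. Smoking rate is also needed at the start of treatment: "The nicotine patch and lozenge regimens are based on each participant’s self-reported smoking rate".

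The longitudinal abstinence model is a GEE "with the main covariates of treatment group, time (months from baseline), and the interaction of group and time". The same paragraph then adds any covariate on which the arms differ at p < .10. General analytic approach states that screen as well, there for the primary analyses. The paragraph closes with the sentence that reaches CPD: "Comparable models will be applied to evaluate treatment differences for secondary outcomes".

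No section names baseline CPD as a covariate to be included regardless of the screen, and none says whether the baseline value is a response at time 0.

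**The concern.** Abstinence has almost no baseline information to adjust for, because everyone enters as a smoker. CPD does. Eligibility starts at "self-report of smoking ≥ 1 cigarette in past 30 days", and the nicotine replacement section distinguishes people above and below 10 cigarettes a day, so baseline consumption is likely to vary widely. Some of the follow-up spread will then be between-person difference that the trial has already measured.

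Adjustment gains precision because baseline and follow-up values are correlated, not because the arms happen to differ at baseline. A screen on observed imbalance therefore selects on the wrong property: it will usually leave out a prognostic baseline value. At stake is the chance of detecting a real reduction in smoking on a secondary outcome, at no saving elsewhere.

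**Working it through.** **Inputs from the article.** 170 per group, 1:1 allocation, two-sided alpha 0.05, covariate screen at p < .10, follow-ups at 3, 6, 12, 18 and 24 months. The article gives no SD, effect size, power or correlation for CPD. The baseline-to-follow-up correlation ρ and a starting power of 80% for CPD are assumptions below.

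**1. The plan's own power figure.** For 16% against 29% abstinence, the pooled proportion is 0.225 and

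power = Φ((0.13·√170 − 1.96·√(2·0.225·0.775)) / √(0.16·0.84 + 0.29·0.71)) = Φ((1.695 − 1.157)/0.583) = Φ(0.92) = 0.82.

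The stated power of at least 0.80 reproduces. It concerns abstinence and does not bear on CPD.

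**2. How often the screen admits baseline CPD.** Under randomisation a baseline test at p < .10 is met in about 10% of trials. A simulation with 170 per arm and 20,000 replicates under simple randomisation gave 10.1%. Stratifying on daily versus nondaily smoking should lower this, since that factor is related to CPD.

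**3. Gain from always adjusting, one follow-up.** The variance ratio is 1 − ρ². Adjusted power is Φ((1.960 + 0.842)/√(1 − ρ²) − 1.960).

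| ρ (assumed) | Variance ratio | 80% power becomes | Adjusted N equal to 340 unadjusted |
|---|---|---|---|
| 0.3 | 0.91 | 83.6% | 309 |
| 0.5 | 0.75 | 89.9% | 255 |
| 0.7 | 0.51 | 97.5% | 173 |

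**4. Mean of the five follow-ups.** The hypothesis covers all assessments. Under compound symmetry with the same ρ throughout, V = (1 + 4ρ)/5 and the variance ratio is (V − ρ²)/V. This gives 0.80, 0.58 and 0.36 at ρ = 0.3, 0.5 and 0.7.

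**5. What the p < .10 screen recovers.** In the same simulation, the variance relative to no adjustment was as follows.

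| ρ | Screen | Always adjust | Share of gain recovered |
|---|---|---|---|
| 0.3 | 0.96 | 0.91 | 0.04/0.09, about 44% |
| 0.5 | 0.89 | 0.75 | 0.11/0.25, 44% |
| 0.7 | 0.78 | 0.51 | 0.22/0.49, about 45% |

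Less of this reaches the test, because in about nine trials in ten the model still reports the unadjusted standard error.

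**6. A less favourable setting.** A simulation of 2,000 replicates per setting used skewed baseline CPD (mean about 12), quitters set to zero at 16% and 29%, and an assumed 5% extra reduction among MAPS+ participants who keep smoking. Always adjusting raised power from 16% to 17% at ρ = 0.37, from 24% to 30% at 0.49, and from 37% to 54% at 0.64. At ρ = 0.64 the screen gave 38%.

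**7. If baseline CPD were a time-0 response.** With equal variances, a change-from-baseline contrast has variance 2(1 − ρ) relative to no adjustment: 1.40, 1.00 and 0.60 at ρ = 0.3, 0.5 and 0.7, against 0.91, 0.75 and 0.51 in step 3. An average over time points that includes time 0 is also diluted. A constant effect at five follow-ups with none at baseline averages to 5/6 of its size.

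**The case against.** The strongest reply is that this is a condensed article. One sentence covers five secondary outcomes of different types and cannot be literal, since logistic regression does not fit CPD. Link, distribution and baseline handling may sit in a fuller document that is not shown. That would answer a complaint about missing detail. It does not fully answer this one, because the article does state a covariate rule, and its wording for secondary outcomes carries that rule to CPD.

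Other parts of the reply stand:

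- A reader might infer that the CPD model can hold nothing beyond group, time and their interaction. That is wrong: the p < .10 route is in the same paragraph.
- A reader might infer that each participant's own baseline is certainly ignored. The text does not settle this. Time is counted from baseline, and if baseline CPD is a time-0 response, the group-by-time term uses it. Step 7 shows that this reading would not make up the lost precision.
- A reader might infer bias. An imbalance just under the cut, 1.64 standard errors, would carry about 0.5 × 1.64 = 0.8 standard errors into the follow-up difference at ρ = 0.5. But such imbalance is random, the unadjusted standard error already allows for it, and stratification on daily versus nondaily smoking limits it.
- Every magnitude depends on an assumed correlation, and zeros among quitters can weaken it.

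**Conclusion.** The point holds as a matter of efficiency on a secondary outcome. Under the stated rule, baseline CPD enters in about one trial in ten, probably fewer with the stratification used, and the rule recovers less than half of the variance reduction available.

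If ρ lies between 0.3 and 0.7, always adjusting would bring the variance at one follow-up to between 0.91 and 0.51 of its unadjusted value. With many zeros and a correlation near 0.37, the gain in power may be as little as one percentage point. The documents do not fix where in this range the trial lies. The primary outcome and the sample size are unaffected.

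**What to change.** Add to the analytic plan that the CPD model includes each participant's baseline CPD as a fixed covariate, whatever any baseline comparison shows, with CPD at 3, 6, 12, 18 and 24 months as the response. This also settles that baseline is a covariate and not one of the averaged time points. Name baseline CPD in the imputation model for CPD.

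Take the baseline value from the same item as the follow-up value where one exists. The HSI is scheduled at baseline only, so follow-up CPD must come from another instrument. Table 1 lists the C-TUQ and the smoking status items at both baseline and follow-up, but the article does not say which of them supplies CPD. If no common item exists, use the HSI item.

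The cost is a sentence or two of wording and one model term. Baseline smoking rate is already collected before randomisation, so no participants, visits or assessments are added. The change should be fixed before outcome data are analysed.
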